### Data Collection and Measures

#### Overview

After obtaining informed consent, the project coordinator will administer a baseline assessment to gather sociodemographic, medical, and psychological comorbidities and prior experience with music; review the patient’s treatment history emphasizing previous treatments tried for chronic musculoskeletal pain; and administer measures to assess pain, function, psychological status, and other relevant constructs.

The conceptual framework that informed the choice of study measures is illustrated in Figure 1. The *antecedents* are the patients’ pre-existing conditions that will serve as potential covariates. The music interventions are expected to improve outcomes both directly and indirectly through several theoretically derived *mediators*. During therapist-delivered sessions, more engagement is expected to improve mood, enhance therapeutic alliance, and increase self-efficacy, leading to greater independent practice and use of music [17]. Compared with music listening, the music imagery intervention draws upon a patient’s inner resources (creativity, courage, and serenity) to improve resilience and perceived benefit. The outcomes are based on a biopsychosocial model of pain and include several measures that encompass the biological, psychological, and social dimensions of pain. The mechanistic pathways depicted offer a theoretical framework for the intervention. Although the pilot is insufficiently powered to find significant mediation, pathway testing will be conducted to help inform the future larger RCT.

Assessments will be conducted by video interviews, unless phone or face-to-face interviews are preferred by the veteran. Assessments of similar lengths have been used by the researchers in several previous trials without overburdening the participants. Following each music imagery session, we will collect brief feedback on the content and delivery of the session. To assess immediate posttreatment effects, we will administer a pre-post visual analog scale to assess change in patient-identified symptoms (eg, pain and anxiety).

We will conduct qualitative interviews with up to 20 veterans following the completion of their last session and assessments with a minimum of 8 participants from each music intervention arm. These interviews will assess the participants’ perceptions of the interventions and study participation.

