### Study Innovation

The FAMILIA (Feasibility and Acceptability of Music Imagery and Listening Interventions for Analgesia) study addresses four limitations in music intervention research for chronic pain: few studies in veterans, evaluation of multicomponent music interventions, methodological rigor, and virtual delivery. Most previous studies described a passive, one-session, single-component music listening experience for patients with acute pain [9-13]. In contrast, the FAMILIA study will evaluate 2 music interventions in veterans. Compared with music listening, less is known about multicomponent music interventions, which we hypothesize are more robust in reducing pain owing to greater treatment intensity and more frequent interactions with a music therapist. The FAMILIA study will assess outcomes (feasibility, acceptability, pain, and associated outcomes) of a single-component, minimally interactive intervention (music listening) and a multicomponent, interactive intervention (music imagery).

Systematic reviews of music interventions for pain cite a lack of methodological rigor because of poorly described interventions, a lack of theoretical foundation, and no reporting of adverse events [27,28]. The FAMILIA study will address these methodological concerns in several ways. First, we will adhere to reporting guidelines for music-based interventions developed by Robb et al [29]. Second, we will use a theoretically based conceptual framework (Figure 1) to explore the hypothesized mechanism of action and outcomes. Third, we will systematically monitor for specific potential adverse events in both interventions.

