#### Music Listening Group

In the music listening arm, a music therapist will meet with the veteran once to identify musical tastes, preferences, and activities; musical memories and social influences; and relationships between music, health, and quality of life [42]. From this meeting, an electronic playlist will be compiled for the veteran to listen to during the 12-week treatment period. The veteran will be asked to maintain a music listening log, including how long they listen, what they listen to, and any reactions to the music (eg, benefits and triggers). Music listening time will not be prescribed, but participants will be encouraged to keep track of their listening to music during the week. Our rationale for including the music listening intervention is to explore whether there is a clinically meaningful change in measures and perceived benefits from a less interactive, less intensive music intervention.

A member of the research team will check in with music listening participants (weekly for the first 3 weeks following their initial session, then biweekly following the 1-month assessment [approximately 7 check-ins in total]) to monitor safety, adherence (ie, time listening to music), and identify other issues.

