### Safety and Treatment Fidelity

Listening to music can at times bring up strong emotions, which can increase stress. The potential of this risk is minimal because of the supportive structure of the interventions and the overall study. The therapists are trained to help participants manage any strong emotions that emerge and, if needed, will refer participants for additional psychosocial support.

At each follow-up assessment (1 month, 3 months, and 4 months), a member of the research team will systematically check for participant intercurrent illness, adverse events, and serious adverse events. At all assessments, including baseline, a member of the research team will screen for suicidal ideation guided by a 3-step algorithm consisting of the following: (1) item 9 suicide question of the Patient Health Questionnaire-9 (PHQ-9), (2) the Columbia Suicide Severity Rating Scale Screener if item 9 of PHQ-9 is positive, and (3) Comprehensive Suicide Risk Evaluation for moderate to high risk of suicide based on the Columbia Suicide Severity Rating Scale Screener [43-45].

To ensure intervention fidelity and minimize experimental drift, we will use the following strategies: (1) standardized intervention protocols, study manuals, and training; (2) self-monitoring of intervention sessions recorded in field notes with debriefings across music therapists; (3) quality assurance checklists to track protocol deviations; and (4) therapist field notes documenting session duration and frequency (dose).

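### Adverse events are sought at about 10 stated safety contacts per participant in music listening but 3 in music imagery and usual care, so counts by arm are not comparable

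*Protocol article*

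**What the plan says.** The Study Innovation section of the protocol article presents safety monitoring as one remedy for weak reporting in earlier music trials: "we will systematically monitor for specific potential adverse events in both interventions". Aim 1 Outcomes makes the safety of the music interventions a result of the pilot, to be judged from worsening of pain, depression and anxiety and from any adverse event.

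Two provisions under Safety and Treatment Fidelity apply to all arms:

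- "At each follow-up assessment (1 month, 3 months, and 4 months), a member of the research team will systematically check for participant intercurrent illness"; the same check covers adverse events, whether serious or not.
- A suicide screen has its own schedule: "At all assessments, including baseline, a member of the research team will screen for suicidal ideation guided by a 3-step algorithm".

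Music listening has a further channel. After one meeting with the therapist, a research team member checks in weekly for three weeks, "then biweekly following the 1-month assessment [approximately 7 check-ins in total]) to monitor safety, adherence" and other issues.

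For music imagery, the Overview of Data Collection and Measures lists what is gathered at sessions. After each one, "we will collect brief feedback on the content and delivery of the session". To measure immediate effects, "we will administer a pre-post visual analog scale to assess change in patient-identified symptoms", with pain and anxiety as examples. Safety and Treatment Fidelity adds therapist field notes, listed there as fidelity tools. No section says that adverse events are asked about or recorded at these sessions.

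**The concern.** The number of adverse events found depends on how often, and how directly, participants are asked. Here one music arm has frequent contacts with a declared safety purpose. The other has frequent contacts whose listed content includes no safety question.

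This matters for three reasons. First, safety is a declared Aim 1 result for both interventions, and readers will set the arms side by side. Second, Strengths and Limitations says that the music listening arm was chosen to inform whether the next trial should be a comparative effectiveness trial, so the relative tolerability of the two interventions is something this pilot will be read for. Third, the risk that the article names is strong emotion that raises stress. A passing reaction of that kind during a session may not be recalled at an assessment weeks later.

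**Working it through.** **Inputs.** Music listening: 3 weekly check-ins, then one every two weeks after the 1-month assessment, about 7 in total, in a 12-week treatment period (Music Listening Group). Music imagery: 8 weekly sessions, with up to 12 weeks allowed for rescheduling (Music Imagery Group). All arms: 3 adverse event checks after baseline (Safety and Treatment Fidelity). Planned arm sizes: about 30, 15 and 15 (Study Design).

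**1. Reproduce the stated figure of about 7.** With the 1-month assessment at week 4, biweekly check-ins fall at weeks 6, 8, 10 and 12, so 3 + 4 = 7. With one month taken as 4.35 weeks, they fall at weeks 6.35, 8.35 and 10.35, and a fourth at 12.35 lies just past week 12. That gives 3 + 3 = 6, or 7 if the period runs to week 13. The stated figure is reproduced. The number between the 1- and 3-month assessments is 3 to 4.

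**2. Music imagery sessions in the same interval.** Weekly sessions starting in week 1 fall at weeks 1 to 8, and those after week 4.35 are at weeks 5, 6, 7 and 8, which is 4. Starting at week 0, they fall at weeks 0 to 7, and those after week 4.35 are at weeks 5, 6 and 7, which is 3. So 3 to 4 sessions lie between the two assessments on the planned weekly schedule. Rescheduling would move more of them there. Even spacing over 12 weeks would give 5 to 6, but that is not the plan.

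**3. Length of the interval.** 2 months × 4.35 = 8.7 weeks.

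**4. Contacts after baseline, per participant.**

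| | Music imagery | Music listening | Usual care |
|---|---|---|---|
| Therapist sessions | 8 | 1 | 0 |
| Check-ins with stated safety purpose | 0 | about 7 | 0 |
| Common adverse event checks | 3 | 3 | 3 |
| All planned contacts | 11 | about 11 | 3 |
| Contacts with stated safety purpose | 3 | about 10 | 3 |

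The ratio of stated safety contacts is 10 / 3 = 3.3. Across the arms, if everyone attends, that is 30 × 3 = 90 in music imagery, 15 × 10 = 150 in music listening and 15 × 3 = 45 in usual care.

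**5. What is ascertained equally.** Table 1 schedules the pain rating, PHQ-9 and GAD-7 at baseline, 1, 3 and 4 months, with no arm excepted. Worsening of pain, depression or anxiety defined from those scores can be compared across arms. The imbalance affects events that come to light by being asked about or volunteered.

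**The case against.** A reader might infer that the monitoring promised for both interventions is not carried out in music imagery. The article does not support that. The promise sets no frequency and does not say that contacts will be equal. The checks at 1, 3 and 4 months, the suicidal ideation screen and the symptom scores cover every arm. Music imagery participants are also seen live at each session by a board-certified therapist, and therapists are trained to help with strong emotions and to refer. This objection stands in full: the issue is comparability, not absence of monitoring.

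The difference also has a reason. Music listening is unsupervised after one meeting, and the check-ins supply contact that it would otherwise lack. As the table shows, total planned contacts in the two music arms are about equal. That explains the schedule, but it does not make the counts comparable, since only one arm's extra contacts are said to ask about safety.

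It can also be said that a journal article condenses, and that adverse event recording at sessions may be set out in the study manuals. That is possible, and one sentence would then settle this part. But the article is not silent here: it states the purpose and frequency of safety contacts in one arm and itemises the session data in the other.

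Finally, no between-arm test of adverse events is announced, and outcomes are to be described rather than tested. That lowers the stakes, but a descriptive table by arm invites the same comparison.

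**Conclusion.** The point holds as one of unequal ascertainment. As described, stated safety contacts number about 10 per participant in music listening and 3 in each of the other arms. Between the 1- and 3-month assessments they number 3 to 4 against none. Counts of adverse events pooled over all contacts would not be comparable, and a higher count in music listening could reflect more asking rather than more harm. That direction is plausible, not certain: therapists may note and report events at sessions, which would raise the music imagery count by an amount the article gives no means of judging.

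The figures assume full attendance, weekly sessions and about 7 check-ins. They count a contact only where a safety purpose is stated.

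Two further inferences should not be drawn. One is that the pre-post scale cannot register distress: the article speaks of symptoms in the plural and names anxiety as an example, and does not say that a participant rates only one. What can be said is that no item is fixed for everyone. The other is that all music imagery sessions go without any safety record; the article simply does not say.

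**What to change.** 1. State whether adverse events are asked about and recorded at music imagery sessions. If they are not, add the safety questions used at the music listening check-ins to the feedback already collected after each session. This needs no new visits or staff. The cost is about a minute per session.
2. Report adverse events found at the common 1-, 3- and 4-month assessments separately from those found at arm-specific contacts, and use only the former for any comparison between arms. This is still needed after step 1, because usual care has no arm-specific contacts. It requires recording the contact at which each event was found. Its limit is that events raised only at sessions or check-ins are left out of the comparison, though they are still reported within their arm.
3. Optionally, add one distress line, the same for every participant, to the pre-post scale, so that change in distress over a session can be summarised for the whole music imagery arm. The first two steps do not depend on it.

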#### Aim 1 Outcomes

Feasibility metrics include recruitment, retention, completion in allotted time (eg, 12 weeks for the music imagery group), and completion of assessments. The goal is to recruit and enroll 60 veterans into the pilot trial and to complete a median of 80% of all study visits. Those who miss visits will be called upon to ask about barriers to attendance. Individuals who dropped out of the study will be asked what could have been done to improve their participation. music imagery sessions will occur weekly on a fixed schedule while allowing some flexibility in scheduling for the participant’s convenience. The proportion of music imagery participants who complete all sessions within the treatment period will be measured. On the basis of the previous trials, the expected completed outcome assessments rate is 85%.

Acceptability of randomization to study groups will be tracked. Treatment credibility will be assessed for each music intervention and veterans’ treatment satisfaction, experience of the interventions, benefits, and barriers or facilitators to study participation will be gathered through qualitative interviews at the end of the treatment period. Safety of the music interventions will be assessed by tracking exacerbations of pain, depression, anxiety, and any adverse events.

#### Aim 2 Outcomes

The selected measures for aim 2 are outlined in Table 1. The choice of measures is informed by the Initiative on Methods, Measurement, and Pain Assessment in Clinical Trials recommendations, our previous studies, the biopsychosocial model, Creative Forces Network’s conceptual framework for music therapy, and constructs hypothesized to be affected by the interventions [37].

**Table 1 table1:** FAMILIA (Feasibility and Acceptability of Music Imagery and Listening Interventions for Analgesia) patient-centered outcomes: measures and schedule of administration.

Domain		Measure	Schedule							
			BL^a^		1 month		3 months		4 months	
**Antecedents**										
	Covariates	Demographics, military history, disability compensation, comorbidity, pain treatments	✓^b^							
**Potential mediators**										
	Therapeutic relationship	Working Alliance Inventory					✓			
	Inner resources	State-Trait Assessment of Resilience Scale	✓		✓		✓		✓	
	Self-efficacy	Arthritis Self-Efficacy Scale	✓				✓			
**Outcomes**										
	Pain intensity	Numeric Rating Scale	✓		✓		✓		✓	
	Pain interference	Brief Pain Inventory-interference	✓		✓		✓		✓	
	Pain beliefs	Brief Pain Catastrophizing Scale	✓				✓			
	Pain coping	Centrality of Pain Scale	✓				✓			
	Pain treatment response	Patient Global Impression of Change			✓		✓		✓	
	Sleep	PROMIS^c^ Sleep Scale	✓		✓		✓		✓	
	Depression	PHQ-9^d^ Depression	✓		✓		✓		✓	
	Anxiety	GAD-7^e^ Anxiety	✓		✓		✓		✓	
	Trauma	PC PTSD^f^ Screen	✓							
	Stress	Perceived Stress Scale	✓				✓			
	Generic HRQL^g^	EQ-5D	✓				✓			
	Social support	Brief Social Support Scale	✓							

^a^BL: baseline.

^b^Check marks indicate when the measure is performed.

^c^PROMIS: Patient-Reported Outcomes Measurement Information System.

^d^PHQ-9: Patient Health Questionnaire-9.

^e^GAD-7: 7-item Generalized Anxiety Disorder.

^f^PC PTSD: primary care posttraumatic stress disorder.

^g^HRQL: health-related quality of life.

#### Brief Description of Proposed Measures for FAMILIA Pilot Study

##### Potential Mediators

The following measures were chosen to explore potential mechanistic pathways for the intervention:

Working Alliance Inventory: the Working Alliance Inventory is a measure of the therapeutic alliance that assesses three key aspects of the therapeutic alliance: (1) agreement on the tasks of therapy, (2) agreement on the goals of therapy, and (3) development of an affective bond [46].State-Trait Assessment of Resilience Scale: this new measure assesses resilience with a state and trait approach. Early studies suggest that the State-Trait Assessment of Resilience Scale is a useful measure to track and predict an individual’s resilience [47].Arthritis Self-Efficacy Scale: this 8-item scale proved sensitive to change in our trial of low back pain. For each item, patients reported their degree of certainty on a scale ranging from 1 (very uncertain) to 10 (very certain) [48].

##### Outcomes

The following outcome measures encompass the biological, psychological, and social dimensions of pain:

Numeric Rating Scale: this pain intensity scale uses a 0 to 10 numeric rating scale that is anchored with “0”=no pain and “10”=the worst pain imaginable. The Numeric Rating Scale has been validated for specificity and use in chronic pain research [49].Brief Pain Inventory (BPI): the BPI is a multidimensional pain measurement tool with demonstrated reliability in patients with arthritis and other pain conditions. The BPI rates the intensity of pain as well as the interference of pain with mood, physical activity, work, social activity, relationships with others, sleep, and enjoyment of life [50].Brief Pain Catastrophizing Scale: this new brief version of the Pain Catastrophizing Scale has been derived and shows sound measurement properties and strong association with the full 13-item original scale [51].Centrality of Pain Scale: the Centrality of Pain Scale is a 10-item self-report instrument. Responses are measured on a 5-point Likert scale ranging from “strongly disagree” to “strongly agree.” In its original validation study, the scale demonstrated high internal consistency (Cronbach α=.90) and good construct validity [52].Patient Global Impression of Change: this is a 15-point, well-validated, global rating scale for evaluating changes in symptoms over time. This scale asks patients to make an initial global assessment of change in their symptoms as “worse,” “about the same,” or “better.” Those who respond that they are “worse” or “better” are asked to make an additional global rating [53].The Patient-Reported Outcomes Measurement Information System Sleep Scale: the Patient-Reported Outcomes Measurement Information System Sleep Disturbance Scale assesses sleep quality and depth, along with difficulties and satisfaction with sleep. Scores are standardized to the general United States adult population on the T-scale with a mean of 50 and SD of 10. Higher scores indicate more symptoms being assessed. A clinically meaningful difference is considered to be ≥5 points [54].PHQ-9 depression: several studies have validated the PHQ-9 as a diagnostic measure with excellent psychometric properties. Internal consistency has consistently been shown to be high (Cronbach α>.80), and test-retest assessment showed the PHQ-9 to be a responsive and reliable measure of depression treatment outcomes [43].7-item Generalized Anxiety Disorder-Anxiety: the 7-item Generalized Anxiety Disorder has demonstrated reliability (Cronbach α=.89) and validity (criterion, construct, and factorial) as a measure of anxiety in the general population and in primary care [55].Primary Care PTSD Screen: the Primary Care PTSD Screen for the Diagnostic and Statistical Manual of Mental Disorders, Fifth Edition is used as a screening measure, and is a modified version of the PTSD module of the MINI-International Neuropsychiatric Interview to diagnose Diagnostic and Statistical Manual of Mental Disorders, Fifth Edition PTSD. It has demonstrated strong preliminary results for diagnostic accuracy [56].Perceived Stress Scale: the 10-item Perceived Stress Scale is the most widely used psychological instrument for measuring the perception of stress and has been used in previous music trials [57].EQ-5D-5L: the EQ-5D-5L questionnaire is an instrument for describing and valuing health states and has been used in hundreds of trials. It is a brief self-reported measure of generic health that consists of 5 dimensions (mobility, self-care, usual activities, pain or discomfort, and anxiety or depression), each with 5 levels of functioning [58].Brief Social Support Scale: this reliable and valid short (6-item) scale assesses the emotional and practical dimensions of social support [59].

### Data Analysis

As an RCT, it is expected that baseline characteristics of the study participants will be balanced across the 3 treatment groups; however, possible group imbalances will be assessed. Outcomes (feasibility, acceptability, pain, and other patient-centered outcomes) will be reported as means with SDs for continuous variables, or medians (IQRs) for nonlinear data and frequencies with percentages for categorical variables. Changes in pain, associated patient-centered outcomes, and proximal and distal mediators will be explored from baseline to follow-up assessments (1, 3, and 4 months). Bivariate analyses will be performed first to determine if there are significant differences in the 3 treatment groups for the antecedent, mediator, and outcome variables, which will also help to determine if there are group imbalances as discussed above. These analyses will be performed using ANOVA and chi-square tests for continuous and categorical variables, respectively. No post hoc *P* value adjustments will be made, as this is a feasibility study. Data transformations will be used if necessary and Fisher exact test will be used instead of chi-square when expected cell counts are small, with data analyses being performed using SAS software (version 9.4; SAS Institute [60]). Path analyses will then be performed to examine the path coefficients for the entire conceptual study model (Figure 1). The path coefficients, model fit indices, and covariance structures, along with the results from the bivariate analyses, will be used to determine model adjustments and parameter estimates necessary to determine the power for a larger full study. Path analyses will be performed using Mplus (version 8.7; Muthén & Muthén [61]).

Using guidelines from the thematic analysis by Braun and Clarke [62], the qualitative analysis of veteran interviews and music imagery participant listening logs will occur in 2 broad phases: open coding and focused coding. Open coding facilitates development of a code list for further analysis. In this phase, selected transcripts are read to gain a general understanding of the data and variation across participants. Then, each line will be independently labeled with initial codes to describe the data. The research team will meet to discuss and compare initial codes. The team will then examine the codes, looking for emerging categories to sort and organize the data. As new transcripts are reviewed and coded, categories may be altered or codes are restructured within the categories. This process will occur iteratively until agreement on, and shared understanding of, emergent thematic categories is established. In phase 2, focused coding, the categories derived in the first phase will be applied to transcripts. A subset of transcripts will be coded by all analysts using the agreed-upon categories. Team members will meet in pairs to ensure coding consistency, with discrepancies resolved by consensus. Representative quotations will be presented for each category.

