**Methods:**

FAMILIA (Feasibility and Acceptability of Music Imagery and Listening Interventions for Analgesia) is a 3-arm, parallel group, pilot trial. A total of 60 veterans will be randomized to one of the three conditions: music imagery, music listening, or usual care. Aim 1 is to test the feasibility and acceptability of a multicomponent, interactive music imagery intervention (8-weekly, individual sessions) and a single-component, minimally interactive music learning intervention (independent music listening). Feasibility metrics related to recruitment, retention, engagement, and completion of the treatment protocol and questionnaires will be assessed. Up to 20 qualitative interviews will be conducted to assess veteran experiences with both interventions, including perceived benefits, acceptability, barriers, and facilitators. Interview transcripts will be coded and analyzed for emergent themes. Aim 2 is to explore the effects of music imagery and music listening versus usual care on pain and associated patient-centered outcomes. These outcomes and potential mediators will be explored through changes from baseline to follow-up assessments at 1, 3, and 4 months. Descriptive statistics will be used to describe outcomes; this pilot study is not powered to detect differences in outcomes.

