**Aims and Questions**
Study aim 1: test the feasibility and acceptability of a multicomponent, interactive music imagery intervention and a single-component, minimally interactive music listening intervention.What percentage of veterans consent to study participation, attend intervention sessions, and complete the treatment protocol and scheduled outcome assessments?What are veteran experiences with both interventions?What aspects of the interventions do veterans perceive to be most or least helpful and most or least liked?What are barriers and facilitators to study participation?How did the music interventions compare to other chronic pain treatments already tried?Study aim 2: explore the effects of both music interventions (music imagery and music listening) vs usual care on pain and associated patient-centered outcomes.What are the changes from baseline to follow-up assessments (1, 3, and 4 months) on pain and associated patient-centered outcomes?What are the changes in proximal and distal mediators, and do they vary based on group assignment?What proportion of veterans achieve a clinically meaningful change in pain intensity and pain interference?

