### Potential Results and Interpretations

There are several potential results and interpretations from the trial. It is expected that both music interventions will prove acceptable to veterans and that feasibility benchmarks will be reached. However, it is possible that one or both music interventions will not be embraced by all participants or may not meet all specified benchmarks. The qualitative interviews will identify the range of participant perceptions and experiences of both interventions and provide insight into the reasons for unacceptability or feasibility concerns. Although it is hypothesized that both music interventions will be more effective than usual care on pain and associated outcomes, differences in outcome scores may be observed but are unlikely to reach stochastic significance (because FAMILIA is not powered to evaluate efficacy). This potential scenario is acceptable in the context of pilot clinical trials where the primary objective is to field-test logistical aspects of the future RCT and to incorporate these aspects into the study design.

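### Unadjusted three-group significance tests are the first analysis step, double as the baseline balance check and feed the next trial's planning, in a pilot that calls itself unpowered to detect differences

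*Protocol article*

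**What the plan says.** The Methods part of the abstract states: "Descriptive statistics will be used to describe outcomes; this pilot study is not powered to detect differences in outcomes". The section Potential Results and Interpretations expects the same: "differences in outcome scores may be observed but are unlikely to reach stochastic significance (because FAMILIA is not powered to evaluate efficacy". Study aim 2 in Textbox 1 is to "explore the effects of both music interventions (music imagery and music listening) vs usual care" on pain and associated outcomes.

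The Data Analysis section opens with descriptive reporting (means and SDs, medians and IQRs, percentages). It then adds testing: "Bivariate analyses will be performed first to determine if there are significant differences in the 3 treatment groups for the antecedent, mediator, and outcome variables". The same sentence says this will help to show whether the groups are imbalanced. The method follows: "These analyses will be performed using ANOVA and chi-square tests for continuous and categorical variables, respectively". The P values are left uncorrected for multiplicity, and the feasibility purpose of the trial is given as the reason.

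Modelling comes next: "Path analyses will then be performed to examine the path coefficients for the entire conceptual study model". Finally, the section lists what the modelling yields (coefficients, fit statistics and covariances) and says that these, "along with the results from the bivariate analyses, will be used to determine model adjustments and parameter estimates necessary to determine the power" of the larger study.

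**The concern.** There are three separate difficulties.

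- **Role of significance.** The plan expects outcome differences not to reach significance, yet makes significance its first question and carries the answer forward. In a small trial, tests miss real effects and, over many measures, turn up chance ones.
- **Baseline testing.** After proper randomisation, any baseline difference is due to chance, so a P value for it answers a question already settled. It does not tell the reader whether an imbalance is large enough, on a prognostic enough variable, to distort a comparison.
- **Wrong contrast.** A three-group test asks whether the arms differ anywhere. Aim 2 asks about each music arm against usual care, and the next trial needs an estimate and an SD for those contrasts.

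At stake are the reading of Aim 2 and the inputs to the next trial.

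**Working it through.** The article states no alpha, effect size, SD or power for these tests, so there is no figure to reproduce beyond the split: 60 in ratio 2:1:1 gives 60 × 2/4 = 30, 60 × 1/4 = 15 and 15, as stated under Study Design. Everything below assumes a two-sided alpha of 0.05 per test.

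**1. Sensitivity of the baseline test.** Suppose usual care differs from both music arms by d SDs.

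- Noncentrality is λ = [n_UC × (N − n_UC)/N] × d².
- At 30/15/15 with d = 0.5: λ = (15 × 45/60) × 0.25 = 2.81. The critical value of F(2, 57) is 3.16. The noncentral F distribution gives power of 29%.
- For other shifts at 30/15/15, power is 8% (d = 0.2), 13% (d = 0.3) and 64% (d = 0.8).

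So about seven in ten imbalances of half an SD would pass as not significant. The same calculation applies to a follow-up outcome. With the 85% assessment completion expected under Aim 1 Outcomes (60 × 0.85 = 51, taken as 25/13/13), λ = (13 × 38/51) × 0.25 = 2.42 and power is 25%.

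**2. Number of tests.** Table 1 is a schedule of measurement, and the article does not say that every measure is tested at every visit. If it were, the post-baseline count would be:

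- Mediators: Working Alliance Inventory 1, resilience 3, self-efficacy 1 = 5.
- Outcomes: pain intensity 3, pain interference 3, catastrophizing 1, centrality of pain 1, global impression of change 3, sleep 3, depression 3, anxiety 3, stress 1, EQ-5D 1 = 22.
- Total 27, or 26 without the Working Alliance Inventory, which is hard to apply in usual care because that arm has no study therapist.

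**3. Chance of at least one false positive.** For k independent tests it is 1 − 0.95^k.

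- k = 26: 1 − 0.95^26 = 0.74, with 26 × 0.05 = 1.30 expected.
- k = 27: 1 − 0.95^27 = 0.75, with 27 × 0.05 = 1.35 expected.

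The scales are related and repeated, so independence is the upper end. Simulated ANOVAs at 30/15/15 with equal correlation between tests (40,000 runs each) give:

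| Correlation | 26 tests | 27 tests |
|---|---|---|
| 0.3 | 63% | 64% |
| 0.5 | 49% | 50% |
| 0.7 | 34% | 34% |

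**4. What follows if significance picks the planning values.** For imagery versus usual care (30 v 15), a t test reaches P<0.05 only if the observed difference is at least 2.017 × √(1/30 + 1/15) = 0.64 SD. In simulation (40,000 runs), results passing that filter overstate a true 0.5 SD effect about 1.7-fold and a true 0.3 SD effect about 2.7-fold. This is conditional: the article does not say that planning values will be picked that way.

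**5. What the contrasts would show.** With complete data and no covariate adjustment, the 95% half-width is 2.002 × √(1/n₁ + 1/n₂) SDs. For imagery minus usual care this is 2.002 × 0.316 = 0.63 SD, and for listening minus usual care 2.002 × 0.365 = 0.73 SD. The intervals are wide, and they show the uncertainty that a non-significant omnibus P value conceals.

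**The case against.** The abstract does not say that outcomes will be described and nothing more. The Data Analysis section does give the descriptive summaries and then adds exploratory tests, openly unadjusted, which is acceptable in a pilot. The power limits are stated repeatedly. This stands: the mismatch is one of emphasis and use, and the missing multiplicity adjustment is not itself the fault.

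A reader might infer that covariates will be chosen by P value, or that only significant effects will go forward. The text supports neither. The antecedents are named as potential covariates from the conceptual framework, the path model is the whole of that framework, and the bivariate results are one input among several. The phrase on model adjustments can mean the pilot model or the future one. What stands against the plan is that, on either reading, the test results inform a decision.

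It is also fair that Aim 2 asks whether mediator changes vary by group, which a three-group test does address, and that pairwise differences can be derived from arm means and SDs. But the plan does not commit to presenting those differences or their intervals.

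Lastly, unadjusted confidence intervals carry the same multiplicity as unadjusted tests. This is true, so they too must be labelled exploratory. Their gain is that they report size and uncertainty for the right contrast.

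**Conclusion.** The point holds in limited form. The plan puts unadjusted omnibus tests first, uses them to judge randomised balance, and passes their results on to the next trial's planning, while stating that the pilot is not powered to detect differences. As a balance check, the test detects a 0.5 SD shift in usual care only about 29% of the time. As an outcome analysis, it does not estimate the Aim 2 contrasts. The multiplicity figure runs from about 34% to 75%, depending on correlation, and rests on an assumed alpha of 0.05 and on 26 or 27 tests that the article does not itself specify. Aim 1, the stated primary purpose, is untouched. This is a worthwhile improvement to the exploratory analysis and not a threat to the trial.

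**What to change.** - Present the baseline table by arm without P values, and judge imbalance by its size and likely prognostic weight.
- Replace the omnibus outcome tests with music imagery minus usual care and music listening minus usual care estimates and 95% confidence intervals, labelled exploratory. Adjust for sex (the stratification factor) and for the baseline value where Table 1 collects one.
- Patient Global Impression of Change and the Working Alliance Inventory have no baseline, so do not adjust them for one. Compare the Working Alliance Inventory only between the arms that have a study therapist.
- Set the path-model covariates in advance from the conceptual framework.
- Take planning parameters from these estimates and SDs with their intervals, not from whether a test was significant.
- Align the wording of the abstract and the Data Analysis section, so that both describe descriptive summaries plus exploratory estimates.

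Sample size, visits and data collection do not change. The cost is rewording, somewhat different tables and the loss of exploratory P values.
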